## Abstract

**Background:**

Methotrexate (MTX) is recommended as first-line therapy in patients with rheumatoid arthritis (RA), proven to be effective, safe and inexpensive. However, a significant proportion of patients does not achieve disease remission with MTX monotherapy. Main reasons include insufficient dose up-titration to the maximal recommended oral dose or the delayed switch to a subcutaneous administration route. We hypothesise, that by dose and route optimisation, a higher proportion of patients can achieve remission. Further, exploratory biomarkers will give new insights on individual MTX metabolism and drug adherence.

**Methods:**

The MethMax trial is a prospective, randomised, assessor-blinded, parallel-group, superiority, low-intervention trial, including 182 patients across 7 European countries. Patients with active RA, naïve to biologic (except tumour necrosis factor alpha inhibitors; TNFi) or targeted synthetic antirheumatic drugs, who have been on a stable oral MTX therapy for the past 3 months are randomised in a 1:1 ratio to 25 mg MTX weekly, either administered orally or subcutaneously. Additionally, both arms receive a short-term glucocorticoid regimen with a four-week tapering and withdrawal protocol. The primary endpoint is the difference in proportion of patients achieving remission defined as the Clinical Disease Activity Index (CDAI) ≤ 2.8 at week 24, comparing the dose/route optimisation and oral dose optimisation. The active study duration for each patient is 24 weeks. Study visits take place at baseline, weeks 4, 12, 16 and 24. Clinical efficacy and safety parameters are obtained at each visit. Patient-reported outcomes, exploratory biomarkers as well as medication adherence are assessed. Written consent is obtained for all participants. The study has received regulatory approval via the Clinical Trials Information System and Medicines and Healthcare products Regulatory Agency and has included the first patient in August 2024.

**Discussion:**

The anticipated results will provide insights whether the subcutaneous administration of 25 mg MTX is advantageous in achieving CDAI remission when compared to the oral intake after 24 weeks and inform the community regarding the utility of established and newly developed biomarkers, as well as the potential impact of inadequate drug adherence.

The MethMax study is aimed to optimise individual therapy in RA and provide more precise pharmacological MTX management recommendations.

Health Condition(s) or Problem(s) Studied	Rheumatoid Arthritis
Intervention(s)	Adapting the ongoing methotrexate therapy to either 25 mg subcutaneously once weekly or 25 mg orally once weekly
Key Inclusion Criteria	Adult patients diagnosed with rheumatoid arthritis who have active disease, at least one swollen joint and have been receiving stable MTX therapy at a dose of 10–25 mg for a minimum of 3 months.
Key Exclusion Criteria	1. Inflammatory rheumatic diseases other than RA 2. Ongoing or previous therapy with any targeted synthetic DMARDs (tsDMARD) or biological Disease-Modifying Anti-Rheumatic Drug (bDMARD) with the exception of any TNFα inhibitor in a stable dose and interval for at least 4 months; We allow ongoing or previous therapy with a conventional synthetic DMARD (csDMARD) with a stable dose in the past 4 months. 3. Use of GC unless on stable oral dose ≤ 10 mg for at least 4 weeks prior to study inclusion 4. Patients using NSAIDs, unless taken at a stable dose for ≥ 2 weeks prior to study inclusion 5. Intraarticular GC treatment in the last 8 weeks 6. Patients with significant and clinically relevant MTX-drug toxicity as judged by the investigator Further exclusion criteria define organ function thresholds, infections, vaccinations, participation in studies and other (full list is provided in section 14a).
Study Type	Prospective, international, multicentre, randomised, assessor-blinded, parallel-group, superiority, low intervention study Phase IV
Date of First Enrollment (planned)	12-Aug-2024
Sample Size	182
Primary outcome(s)	The primary endpoint is the achievement of remission defined as the CDAI ≤ 2.8 assessed 24 weeks after randomisation comparing patients with dose/route optimisation (≥ 10 mg MTX oral weekly switched to 25 mg MTX subcutaneously weekly) and oral dose optimisation (≥ 10 mg MTX oral weekly switched to 25 mg MTX oral weekly).
Key Secondary outcome(s)	The proportion of patients achieving CDAI low disease activity, American College of Rheumatology (ACR) scores ACR20, ACR50, ACR70, patient reported outcomes and inflammatory markers across different timepoints. Exploratory endpoints include assessment of methotrexate-polyglutamates (MTX-PGs), sweat metabolites, treatment adherence, safety parameters and cumulative glucocorticoid dose.
Ethics Review	Each country specific ethics review was processed via CTIS, identifier EU-CT Number 2023–507714-27–00. In detail, the Ethics Committee of the Medical University of Vienna was responsible for review of the main trial sponsor site, Medical University of Vienna.
Individual Trial Participant Data sharing statement	Deidentified individual trial participant data can be provided upon reasonable request.

## Protocol version {2}

Version 2.0, 16th May 2025.

## Introduction

### Background and rationale {9a, b}

Methotrexate (MTX) is recommended as the disease-modifying antirheumatic drug (DMARD) of choice in patients newly diagnosed with rheumatoid arthritis (RA) [1]. It is considered an anchor drug for RA given its well-established and balanced efficacy, safety and tolerability profile, but also its relative affordability. MTX is a folic acid analogue whose immunomodulatory effects are mediated through multiple mechanisms, including inhibition of folate-dependent enzymes such as dihydrofolate reductase and ATIC (AICAR transformylase), leading to intracellular AICAR accumulation and increased extracellular adenosine release [2, 3]. Furthermore, concomitant folate substitution provides increased safety and reduces side effects [4]. Despite all its advantages, achieving long-term remission with MTX monotherapy is only limited to a minority of RA patients [5]. The main known limitations in clinical long-term use of this drug are (a) the insufficient titration to the maximum recommended per os (p.o.) dose of 25 mg weekly [6] and (b) the delayed switch to subcutaneous (s.c.) route or an addition of a biologic or targeted synthetic therapy when the oral route is deemed ineffective. Moreover, adherence to MTX might be influenced by relatively common side effects associated with oral administration such as nausea, abdominal discomfort or headache.

Existing studies provided a reasonable basis for s.c. application of MTX (SCMTX) being superior to oral administration (POMTX), leading to improved efficacy [7–9]. SCMTX application showed higher efficacy due to improved bioavailability and reduced side effects (gastrointestinal adverse events (AEs) reduced by 30%) in previous trials [10, 11]. According to the European Alliance of Associations for Rheumatology (EULAR) guidelines for the use of MTX, both MTX dose and route should be optimised to achieve maximum effectiveness, provided no safety concerns arise. This is particularly relevant for patients who have already shown an initial positive response to MTX: such early treatment response may serve as a marker to identify patients who may benefit most from dose or route optimisation [12].

MTX monotherapy is often escalated to a TNFi if MTX alone fails to achieve adequate clinical response or disease control. TNFi, when used in combination with MTX, have demonstrated superior efficacy compared to TNFi monotherapy in the treatment of RA [13, 14]. MTX not only enhances the clinical effectiveness of TNFi but also helps reduce the formation of anti-drug antibodies (ADAs), thereby improving drug persistence and treatment durability [15–17]. The concomitant use of MTX is particularly important in maintaining therapeutic drug levels, minimising immunogenicity, and delaying secondary loss of response. This combination strategy has become a cornerstone in optimising biologic therapy outcomes.

The metabolic pathway of MTX is complex. In hepatocytes, aldehyde oxidases convert MTX to 7-hydroxymethotrexate (7-OH-MTX), a metabolite that has been proposed to influence MTX efficacy [18]. When transported intracellularly, MTX is converted into active MTX polyglutamates (MTX-PGs) by folylpolyglutamate synthetases, which add glutamate residues to MTX in multiple steps [19]. Importantly, while laboratory measurements of active metabolites (MTX-PGs 1–7) are methodologically challenging, their association with disease activity and patient characteristics is extremely valuable to better understand MTX treatment outcomes. Moreover, MTX-PGs could also be used as adherence measurements for patients with ongoing MTX treatment [20, 21].

Therapeutic drug monitoring (TDM) is applied in multiple clinical fields, e.g. in neuropsychiatric [22] and antimicrobial [23] therapy, as well as in biologic therapy in inflammatory bowel disease [24]. Importantly, however, TDM is insufficiently documented in rheumatic diseases, and the use of proactive TDM is currently not recommended for biological DMARDs (bDMARDs), other than infliximab [17, 25, 26]. This has prompted paramount research in TDM for biologics [26] and synthetic DMARDs [27] in rheumatic diseases.

Finally, we should also consider intra-individual variation of immunosuppression levels, which are influenced by multiple factors, making any quantification difficult. This aspect was recently investigated via measuring peripheral blood levels of torque teno virus (TTV), a virus found in the majority of the healthy adult population, which is associated with rejection and infection in solid organ transplant recipients [28]. Recent data showed a possible use of TTV measurement in patients with RA on bDMARDs to better determine their immunosuppression level [29]. This has prompted us to investigate TTV in this trial, for the first time in patients receiving MTX.

Here, we describe the study protocol of the MethMax trial—which is aimed to evaluate the clinical and biomarker response after optimising the MTX treatment regimen. We hypothesise that in RA patients with active disease despite ongoing MTX treatment, SCMTX is superior to POMTX at weekly dosing of 25 mg after 24 weeks. Furthermore, we want to explore the utility of novel biomarkers (metabolites in blood and sweat) in these patients.

### Objectives {10}

The primary objective is to assess the proportion of patients in CDAI remission (≤ 2.8) at week 24. Among the secondary objectives, we assess the proportion of patients achieving CDAI low disease activity, ACR20, ACR50, ACR70, patient-reported outcomes and inflammatory markers across different timepoints. Exploratory objectives include assessment of MTX-PGs, sweat metabolites, treatment adherence, safety parameters and cumulative GC dose.

## Methods: patient and public involvement, and trial design

### Patient and public involvement {11}

The study aims to enrol 182 patients across 7 European countries, at 7 study sites. Eligible patients need to be classified as having RA based on the ACR/EULAR 2010 classification criteria [30] with ongoing stable oral MTX therapy at a dosage of at least 10 mg/week to a maximum of 25 mg/week for at least 12 weeks. For inclusion, patients need to have active disease as assessed by the CDAI of > 2.8 AND at least one or more clinically swollen joints on a 28-joint count. History of any csDMARD and TNFi and their concomitant use in a stable dosing regimen is allowed. Concomitant treatment with glucocorticoids and non-steroidal anti-inflammatory drugs (NSAIDs) in a stable dosing regimen is allowed as described below.

### Trial design {12}

The MethMax trial is a prospective, international, multicentre, randomised, assessor-blinded, parallel-group, superiority, low intervention trial. The study follows the principles of the International Council for Harmonisation of Technical Requirements for Registration of Pharmaceuticals for Human Use—Good Clinical Practice (ICH GCP), the Declaration of Helsinki and complies with respective country-specific regulations. Before study inclusion, written informed consent is obtained from each participant. The protocol of the MethMax study fulfils the requirements of the SPIRIT statement (Standard Protocol Items: Recommendations for Interventional Trials).

## Methods: participants, interventions and outcomes

### Trial setting {13}

The trial is one of the three clinical trials within the Squeeze project, funded by the Horizon Europe Programme. It has gained regulatory approval in the European Union through the Clinical Trials Information System (CTIS) with the identifier EU-CT Number 2023–507714-27–00 for the following six centres: Medical University of Vienna, Vienna, Austria (29th April 2024); Leiden University Medical Centre, Leiden, Netherlands (22nd April 2024); Diakonhjemmet Hospital, Oslo, Norway (22nd April 2024); Karolinska University Hospital, Stockholm, Sweden (25th April 2024); Carol Davila University of Medicine and Pharmacy, Bucharest, Romania (3rd February 2025) and Humanitas Research Hospital, Milan, Italy (9th May 2025). The regulatory approval for Queen Mary University of London (QMUL), London, UK, was granted on 15th April 2025 by the Medicines and Healthcare products Regulatory Agency (MHRA) and the Research Ethics Committee. The trial was registered on ClinicalTrials.gov, with the identifier NCT06649136 at the time of patient enrolment start. The original protocol, version 1.1, was amended to version 2.0 in May 2025 via CTIS and was granted approval in August 2025. The changes to the protocol are summarised in the “Protocol amendments” section.

## Eligibility criteria for participants {14a}

The inclusion criteria are as follows:Men and women, ≥ 18 years of age, capable of understanding and signing an informed consent (including sufficient literacy and proficiency in the local language) and following the study procedures.Patients with RA according to the 2010 ACR/EULAR classification criteria.Ongoing conventional therapy with oral MTX (between ≥ 10 mg and 25 mg weekly) for ≥ 3 months with stable dosing, and clinical and laboratory tolerance of this treatment for at least 12 weeks.CDAI > 2.8 + at least 1 clinically swollen joint (on 28-joint count).Willingness to increase MTX dosing and change the route of administration according to study procedures.

The exclusion criteria are as follows:Inflammatory rheumatic diseases other than RA.Ongoing or previous therapy with any targeted synthetic DMARDs (tsDMARD) or biological Disease-Modifying Anti-Rheumatic Drug (bDMARD) with the exception of any TNFα inhibitor in a stable dose and interval for at least 4 months. We allow ongoing or previous therapy with a conventional synthetic DMARD (csDMARD) with a stable dose in the past 4 months.Use of glucocorticoids (GC) unless on stable oral dose ≤ 10 mg for at least 4 weeks prior to study inclusion.Patients using NSAIDs, unless taken at a stable dose for ≥ 2 weeks prior to study inclusion.Intraarticular GC treatment in the last 8 weeks.Patients with significant and clinically relevant MTX-drug toxicity as judged by the investigator.Elevated liver enzymes (aspartate transaminase (AST) and/or alanine transaminase (ALT)), and/or alkaline phosphatase (AP), and/or gamma-glutamyl transferase (GGT) above two times the upper limit normal (ULN).Reduced kidney function (glomerular filtration rate (GFR) < 60 mL/min/1.73 m^2^).Haematologic abnormalities (grade 2 or 3: anaemia, leukopenia, thrombocytopenia).Stomatitis under treatment with MTX.Known history of recurrent/serious infections in the previous 2 months (such as, but not limited to, hepatitis, pneumonia, or pyelonephritis).A positive HBs antigen and/or hepatitis C virus (HCV) test at screening visit.Ongoing or recurring opportunistic infections (e.g. herpes zoster, cytomegalovirus, pneumocystis, aspergillosis, histoplasmosis, or mycobacteria) as judged by the investigator.Women of childbearing potential without the use of adequate birth control measures (e.g. abstinence, oral contraceptives, intrauterine device, barrier method with spermicide, implantable or injectable contraceptives or surgical sterilisation) and willing to continue this precaution for the duration of the study until 6 months after receiving the last medication.Current signs or symptoms of severe, progressive or uncontrolled renal, hepatic, haematologic, gastrointestinal, endocrine, pulmonary, cardiac, neurologic, or cerebral disease, as judged by the investigator.Being unable or unwilling to undergo multiple venipunctures because of poor tolerability or lack of sufficient venous access.Being unwilling or unable to perform s.c. injections.Presence of a transplanted solid organ (except for a corneal transplant > 3 months prior to screening).Women who are pregnant, nursing or planning pregnancy during the study and 6 months after the individual study completion.History of alcohol or substance abuse within the preceding 6 months.Any medical or psychological condition that, judged by the investigator, would interfere with the safe completion of the trial.Immunisation with a live/attenuated vaccine within 12 weeks prior to baseline or potential need to receive a live vaccine during the course of the study.Active participation in any other interventional study.

### Who will take informed consent? {32a}

Written informed consent will be obtained by a trained study investigator from all participants prior to any study-specific procedures, after provision of comprehensive verbal and written information about the study and adequate time for discussion.

### Additional consent provisions for collection and use of participant data and biological specimens {32b}

Participants will be asked to provide additional, voluntary consent for the collection and use of health-related data via a mobile application RheumaBuddy. This consent is obtained separately from the main study informed consent and refusal does not affect participation in the study or access to study procedures. Additional voluntary consent is sought for ancillary studies involving optional collection of Peripheral Blood Mononuclear Cells (PBMCs) and storage in local biobanks at participating centres, using centre-specific biobank consent forms.

### Criteria for discontinuing or modifying allocated intervention/comparator {15b}

Criteria for discontinuation or modification of the allocated intervention or comparator include safety concerns, serious or persistent adverse events, pregnancy, protocol deviations affecting participant safety, or investigator judgement. Participants may withdraw consent at any time without consequences for further treatment or study participation.

In case of a worsening of disease activity (CDAI increase > 4.5 compared to baseline) at each visit from week 4 onwards or inadequate improvement of the sum of swollen and tender joints (< 20% change compared to baseline) from week 12 onwards, rescue treatment applies according to standard of care (such as switch or add on of conventional synthetic, biologic or targeted synthetic DMARD (cs/b/tsDMARD)). This results in the participant’s early termination from the study. Non-responder imputation will apply to all patients with a premature end of study.

In case of an AE, a diagnostic or therapeutic procedure, an abnormal assessment (e.g. laboratory abnormalities) the MTX dose can be temporarily interrupted or reduced to ≥ 10 mg/week and re-escalated to 25 mg after resolution of the problem. If drug interruption or intermittent reduction is within a timeframe of ≤ 3 weeks, and re-institution of full dose of the study drug is safe according to the decision of the investigator, no permanent study discontinuation is required.

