### Ancillary and post-trial care {34}

A voluntary follow-up visit occurs 4 weeks after premature discontinuation of the study drug, during which clinical disease activity and relevant laboratory safety and inflammatory parameters are assessed. After completion of the trial, participants return to routine standard-of-care follow-up.

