**Efficacy Assessments**						
Swollen joint count [31]	**x**	**x**	**x**	**x**	**x**	**x**
Tender joint count [31]	**x**	**x**	**x**	**x**	**x**	**x**
Evaluator global assessment (EGA)	**x**	**x**	**x**	**x**	**x**	**x**
Patient global assessment (PGA)	**x**	**x**	**x**	**x**	**x**	**x**
Patient pain assessment (on NRS)	**x**	**x**	**x**	**x**	**x**	**x**
Morning Stiffness (duration and on NRS)	**x**	**x**	**x**	**x**	**x**	**x**
Fatigue (on NRS)	**x**	**x**	**x**	**x**	**x**	**x**
Efficacy assessment CDAI change*			**x**	**x**	**x**	**x**
Efficacy assessment joint count change 20%*				**x**	**x**	**x**
FACIT-Fatigue Questionnaire		**x**		**x**		**x**
Quality of Life Questionnaire SF-36.v1		**x**		**x**		**x**
Disability Scale Questionnaire HAQ-DI		**x**		**x**		**x**
Adherence questionnaire BAASIS-MTX-visit specific		**x**	**x**	**x**	**x**	**x**
RheumaBuddy App use weekly (consent needed)		**x**	**x**	**x**	**x**	**x**
Patient diary MTX and folic acid weekly		**x**	**x**	**x**	**x**	**x**
Patient diary glucocorticoids daily		**x**	**x**	**(x)**	**(x)**	**(x)**

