**Laboratory Assessments**						
Haematology^1^	**x**^^^	**x**	**x**	**x**	**x**	**x**
Serum Chemistry^2^	**x**^^^	**x**	**x**	**x**	**x**	**x**
CRP & ESR	**x**^^^	**x**	**x**	**x**	**x**	**x**
Pregnancy Test^3^	**x**	**x**	**x**	**x**	**x**	**x**
Hepatitis B and C testing^4^	**x**					
RF and anti-CCP^4^	**x**					
MTX-Polyglutamate sampling		**x**	**x**	**x**		**x**
Torque teno virus sampling		**x**	**x**	**x**		**x**
Biobank and PBMC collection optional		**x**	**x**	**x**		**x**
Sweat analysis sampling incl. diary		**x**		**x**		**x**

^*^In case of a disease flare, patient will be transferred to standard of care and an optional safety follow-up visit after 4 weeks will be scheduled

^1^Red blood cell count (RBC), haemoglobin (Hb), haematocrit (Hct), white blood cell count (WBC), platelet count (PLT)

^2^Creatinine (Crea), blood urea nitrogen (BUN), estimated glomerular filtration rate (eGFR), alanine aminotransferase (AST), aspartate aminotransferase (ALT), gamma-glutamyl transferase (GGT), alkaline phosphatase (AP), total bilirubin, albumin

^^^Window for blood assessment −7 days to 0

^3^Blood or urine; in women of childbearing potential at each study visit at the centre and self-reported test in weeks 8 and 20

^4^Within 6 months prior to screening

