## Assignment of interventions: blinding

### Who will be blinded {24a}

Joint assessors performing outcome measurements are blinded to participants’ study assignments. Patients, care providers and personnel performing randomisation are not blinded.

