Overall, the strength of the MethMax trial lies in its study design and procedures, combining multiple objective and subjective measurements of disease activity, patient outcomes and treatment adherence. The efforts to maximise the therapy adherence should deliver more representative results on the true pharmacological effects of MTX in its distinct routes. The main limitations of this study could include recruitment problems due to the relatively stringent inclusion/exclusion criteria, reliance on self-reported and self-performed data, and the impact of daily variations of subjective disease activity, especially in patients with an initial low disease activity score. Furthermore, patients and physicians are unblinded to the treatment allocation, and only joint assessment is performed by blinded personnel.

The anticipated results might bring valuable knowledge about the “maximisation” of the MTX therapy potential in patients with RA, providing recommendations on the optimal dose and administration route.

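### From week 12, the <20% joint-count rescue rule can terminate a patient who is at CDAI ≤ 2.8 and impute failure; a minor gap that one sentence would close

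*Protocol article*

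**What the plan says.** Section {15b} of the protocol article gives two triggers for rescue. One is a CDAI rise of more than 4.5 from baseline, from week 4. The other, from week 12, is "inadequate improvement of the sum of swollen and tender joints", defined as less than 20% change from baseline. Either one leads to rescue under standard of care, such as a DMARD switch or add-on, and to early termination. The section then adds: "Non-responder imputation will apply to all patients with a premature end of study". Section {27c} repeats this imputation for the primary endpoint.

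Entry ({14a}) requires CDAI above 2.8 and "at least 1 clinically swollen joint (on 28-joint count"). The primary endpoint (Table 1) is CDAI ≤ 2.8 at week 24.

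Table 2 schedules the row "Efficacy assessment joint count change 20"% at weeks 12, 16 and 24. The asterisk on that row leads to a footnote: "In case of a disease flare, patient will be transferred to standard of care". Flare is not defined. After termination, section {34} provides this: "A voluntary follow-up visit occurs 4 weeks after premature discontinuation of the study drug".

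**The concern.** The joint criterion is purely relative. It has no minimum joint count and no condition on the CDAI reached. In a patient who enters with one or two counts, an unchanged joint sum is a 0% improvement, even if falling global scores have brought CDAI to the remission threshold.

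Two things would follow for such a patient at week 12 or 16. A patient on target would be sent to a DMARD switch or add-on. The week-24 outcome would also be fixed as failure before it is observed, and it could not be recovered, because the only later visit is voluntary and comes 4 weeks after stopping the drug. The CDAI recorded at that same week-12 visit would meet the definition of CDAI remission at week 12, which is first in the secondary testing sequence of section {27a}.

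**Working it through.** **Inputs.** Entry: CDAI > 2.8 and at least one swollen joint ({14a}), so the baseline joint sum b is at least 1. Endpoint: CDAI ≤ 2.8 (Table 1). Trigger: less than 20% change in the joint sum from week 12 ({15b}). Assumption: CDAI is the usual sum of swollen count, tender count, patient global (0–10) and evaluator global (0–10). Section {25a} lists these components but does not print the formula.

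**Step 1: joint sums compatible with remission.** Let f be the joint sum at the visit. The globals cannot be negative, so CDAI ≤ 2.8 requires f ≤ 2.

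**Step 2: joint sums that trigger the rule.** Reading change as improvement, the rule triggers when (b − f)/b < 0.20, that is, when f > 0.8b.

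- b = 1: f > 0.8, so f = 1 or 2.
- b = 2: f > 1.6, so f = 2.
- b = 3: f > 2.4, so f is at least 3, and CDAI is above 2.8. The same holds for every larger b.

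A drop of one joint is enough to escape: 2 to 1 is 50%, and 3 to 2 is 1/3 = 33%.

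**Step 3: what the globals must do.** The total of the two globals must exceed 2.8 − b at entry and be at most 2.8 − f at the visit.

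| Joint sum | Improvement | Globals at entry | Globals at visit |
|---|---|---|---|
| 1 to 1 | 0% | > 1.8 | ≤ 1.8 |
| 2 to 2 | 0% | > 0.8 | ≤ 0.8 |
| 1 to 2 | −100% | > 1.8 | ≤ 0.8 |

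All three paths can occur. In each of them CDAI has fallen from above 2.8 to 2.8 or below, so the other trigger (a rise of more than 4.5) is not met. The joint criterion alone removes the patient.

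**Step 4: dependence on wording.** If change is taken literally as absolute change, |b − f|/b < 0.20, then 1 to 2 is a 100% change and does not trigger. The paths 1 to 1 and 2 to 2 are 0% and trigger on either reading.

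**Step 5: which visits matter.** At week 24 the endpoint is measured at the same visit, so the conflict is confined to weeks 12 and 16.

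**Sample size.** The planned size is not in question. The stated 76 per group inflated for 16% dropout is 76/0.84 = 90.5, so 91 per group and 182 in total, as section {19} says. The change proposed here does not alter it.

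**The case against.** The strongest reply is that the document at hand is a condensed article. Section {5} says the full protocol is published with it, and an instruction about patients already on target could stand there. That limits the point to the article's text. It does not remove it, because the article states a rule with fixed consequences, and a reader applying it would terminate these patients.

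The second reply is that the article itself hints at a narrower rule. The only footnote on the check refers to flare, section {15b} places rescue within standard of care, and section {15a} treats CDAI ≤ 2.8 as being on target. A patient in CDAI remission is hard to call a flare. This has weight: it makes forced escalation less likely in practice. But the footnote neither defines flare nor lifts the explicit rule, so sites could act differently.

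Third, the improvement in these patients comes wholly from the globals, whereas "only joint assessment is performed by blinded personnel". That is a good reason to watch the joint count. It is a weaker reason to impose failure on someone who meets the endpoint definition, since the primary endpoint uses the same globals.

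A reader might go further and infer that, with remission expected in only 5% and 20% of patients, the rule costs the trial power or biases the comparison. The document does not support that. It gives no distribution of baseline joint counts, so not even one lost remission can be derived. Remission at week 12 or 16 is not remission at week 24. The rule is the same in both arms.

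**Conclusion.** The point holds as a minor defect in the rule as written. For joint sums 1 to 1 and 2 to 2 on any reading, and 1 to 2 if change means improvement, section {15b} requires rescue, termination and imputed failure at week 12 or 16 in a patient at CDAI ≤ 2.8. The Table 2 footnote leaves it unclear whether that is intended.

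The number affected cannot be derived and is probably very small. It needs a baseline joint sum of 1 or 2, no joint improvement, and low globals at the visit; two of the three paths need a globals total of 0.8 or less. Misclassification of week-24 status is possible but not shown, and neither directional bias nor power loss is shown. The conclusion rests on the usual four-item CDAI and on the article's text, without the full protocol.

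**What to change.** Amend section {15b} to say that at weeks 12 and 16 the joint-sum criterion does not trigger rescue or termination when CDAI at that visit is ≤ 2.8. Leave the rule unchanged for everyone else. State that change means improvement from baseline. Reword the Table 2 footnote to refer to the criteria of section {15b} instead of an undefined flare. In the results, report by arm the number of patients already terminated under the joint criterion while at CDAI ≤ 2.8.

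The cost is one short amendment, with no change in sample size. A few patients with an unchanged low joint count will stay on study drug, and whether they stay will depend partly on unblinded globals. Enrolment began in August 2024 and the last patient's first visit is planned for the end of November 2026, so patients before and after the amendment will follow slightly different rescue rules.
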